### 3.6 Plan for Treatment after the End of Study

Further patient treatment will be at the discretion of the Investigator. All patients in re-induction phase when their study period is ending, will be offered free ipilimumab to complete the re-induction treatment. Off-study patients eligible for a re-induction may be treated with ipilimumab if deemed appropriate by the treating physician, either using commercial drug if licensed in Germany or via the Early Access Program if the Marketing Authorization is not granted yet.

## 4 SUBJECT SELECTION CRITERIA

For entry into the study, the following criteria **MUST** be met. Any exceptions from the protocol-specific selection criteria must be approved by the Coordinating Investigator and/or the Institutional Review Board (IRB) before enrollment.

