#### **6.1.1.1. Screening/Baseline Visit**

At the screening/baseline visit, the patient will consent to the study and eligibility will be determined according to the inclusion/exclusion criteria as detailed in Section 4. Patients must meet all inclusion criteria and none of the exclusion criteria to be considered eligible. In addition, a full medical history, prior and ongoing antineoplastic therapies, concurrent medications, and demographic information will be collected. Baseline CT/MRI and photographic imaging will take place at this visit. The following tests and examinations must be performed and the eligibility criteria satisfied before treatment may begin:

**All patients participating in this clinical study with ipilimumab their TSH level must be assessed at baseline and before each dose and the TSH level be available to the investigator prior to the administration of the dose. The assessment of TSH is mandatory prior each treatment.**

- Histologic diagnosis of malignant melanoma, B-RAF status of tumor biopsy
- Demographics and medical history
- Measurements of weight, height, temperature, pulse, respiratory rate, and resting systolic and diastolic blood pressure
- Complete physical examination
- ECOG Performance Status
- Current medications
- Baseline signs and symptoms
- Urine pregnancy test for WOCBP.
- Electrocardiogram (ECG): Patients with an existing myocarditis are excluded from this study.
- Baseline MRT/CT brain and MRT/CT chest/abdomen/pelvis scan was performed. The images can be accepted if obtained 6 weeks before initiation of ipilimumab
- Clinical laboratory tests:
  - Hematology: hemoglobin, CBC counts with differential (including absolute lymphocyte count) and direct platelet count.
  - Serum Chemistry: albumin, CRP, SGOT (AST)/SGPT (ALT), bilirubin (direct and total), creatinine, lactate dehydrogenase (LDH), lipase, electrolytes (including sodium, potassium, chloride, and bicarbonate) TSH, Free T4, S-100
  - Urinalysis (urine dipstick for protein)
- B-Raf Mutational Status and Microtissue Array:

Currently nothing is known whether response to ipilimumab might also be modulated by b-raf mutational status. Therefore Formalin Fixed Paraffin Embedded (FFPE) tissue is requested from every patient. FFPEs blocks from histologically confirmed cutaneous melanoma such as. Primary tumor or subsequent metastases such as lymph node etc. will be eligible.

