#### 9.4. Study population

**Intention to Treat (ITT) = Safety population:** All patients who were enrolled and received at least one dose of ipilimumab.

**Response-evaluable population:** All subjects who were treated with at least one dose of ipilimumab with (i) measurable disease at baseline as determined by the irRC; (ii) histologic diagnosis of malignant melanoma; and (iii) at least one screening (i.e. baseline) and at least one on-study TA.

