#### 9.5. Statistical analysis

The primary endpoint, one year survival rate, is based on the ITT population. As a simple rate, it will be calculated as the number of patients being still alive 12 months after their first administration of the study treatment divided by the number of patients having received at least one administration of the study treatment. Only subjects known to be alive at 1 year will be included in the numerator. As a time to event variable, it will be derived from the Kaplan-Meier curve. In this case missing data will be censored at the last contact. See below for further details.

All other analyses will have exploratory character. Results will be presented overall and per cohort/subgroup:

- (1) cutaneous vs uveal vs. mucosal melanoma
- (2) - LDH < 2 UNL versus LDH ≥ 2 UNL
- (3) - status brain mets versus no brain mets in medical history
- (4) - status Braf mutation positive versus. Braf mutation negative
- (5) - HLA-A2 positive versus HLA-A2 negative

Demographic and baseline characteristics will be tabulated for all treated subjects. For categorical variables, summary tabulations of the number and percentage within each category (with a category for missing data) of the parameter will be presented. For continuous variables, the mean, median, standard deviation, minimum and maximum values will be given.

Proportions (Survival rate at 1 year, irOR, irDCR, irPFS at 6 mths, OR and DCR) will be presented with exact (Clopper and Pearson) two-sided 95% CI. irOR, irDCR and irPFS are defined according to the irRC; OR and DCR according to RECIST; The date of origin for the survival rate at one year, and irPFS at 6 months is the date of the first ipilimumab dose. Only subjects known to be progression free at 6 months / alive at 1 year will be included in the respective numerators. Any subject receiving at least one dose of ipilimumab will be included in the denominators. The denominator for the irOS and irPFS analyses will be the ITT population. The denominator for the irOR, and irDCR, OR and DCR will be the Response-evaluable population..

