### **12.2. Compliance with the Protocol and Protocol Revisions**

The study shall be conducted as described in this approved protocol. All revisions to the protocol must be discussed with Coordinating Investigator, and be prepared by designated person. The investigator should not implement any deviation or change to the protocol without prior review and documented approval/ favorable opinion from the IRB/IEC of an amendment, except where necessary to eliminate an immediate hazard(s) to study subjects. Any significant deviation must be documented in the eCRF. If a deviation or change to a protocol is implemented to eliminate an immediate hazard(s) prior to obtaining IRB/IEC approval/favorable opinion, as soon as possible the deviation or change will be submitted to:

- IRB/IEC for review and approval/favorable opinion
- Regulatory Authority(ies), if required by local regulations

Moreover, Bristol-Myers Squibb will be informed.

Documentation of approval signed by the chairperson or designee of the IRB(s)/IEC(s) must be sent to BMS. If an amendment substantially alters the study design or increases the potential risk to the subject: (1) the consent form must be revised and submitted to the IRB(s)/IEC(s) for review and approval/favorable opinion; (2) the revised form must be used to obtain consent from subjects currently enrolled in the study if they are affected by the amendment; and (3) the new form must be used to obtain consent from new subjects prior to

enrollment. If the revision is an administrative letter, investigators must inform their IRB(s)/IEC(s).

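### Section 4 lets any eligibility criterion be waived on one approval without ethics review, which conflicts with 6.1.1.1 and 8.3.4 and is hard to square with 12.2

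*Protocol*

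**What the plan says.** Section 4 opens with a strict rule: "For entry into the study, the following criteria MUST be met". The next sentence provides a way round it: "Any exceptions from the protocol-specific selection criteria must be approved by the Coordinating Investigator and/or the Institutional Review Board (IRB) before enrollment".

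Three other sections deal with the same question:

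- Section 6.1.1.1 (Screening/Baseline Visit): "Patients must meet all inclusion criteria and none of the exclusion criteria to be considered eligible".
- Section 8.3.4 (Pregnancy): a woman whose pregnancy test is positive may be neither treated nor enrolled.
- Section 12.2 (Compliance with the Protocol and Protocol Revisions): "The investigator should not implement any deviation or change to the protocol without prior review and documented approval/ favorable opinion from the IRB/IEC". What the ethics committee has to approve is a protocol amendment, and the section has a single carve-out, which reads: "except where necessary to eliminate an immediate hazard(s) to study subjects". On recording, it says: "Any significant deviation must be documented in the eCRF".

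On analysis, Section 9.5 states: "The primary endpoint, one year survival rate, is based on the ITT population". Section 9.4 defines that population, which is also the safety population, as: "All patients who were enrolled and received at least one dose of ipilimumab". Eligibility is not a condition.

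**The concern.** A site that has a patient outside one criterion gets two answers from the protocol. Under Section 4 it may enrol the patient once the Coordinating Investigator agrees. Under 6.1.1.1 the patient is not eligible.

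Two things are at stake. The first is the population. The trial has one arm and no concurrent control, so the reader of the 1-year survival rate depends on the selection criteria to know whom it describes. Several criteria are prognostic, such as expected survival of at least six months, ECOG status 0 to 2 and the exclusion of symptomatic CNS metastases. If these can be set aside case by case, the population depends partly on which exceptions were requested and granted.

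The second is protection. Some exclusions are there for safety, for example active autoimmune disease (including a history of inflammatory bowel disease) and pregnancy. Section 4 allows them to be set aside without an ethics committee seeing the request.

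**Working it through.** The main check is textual.

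**1. Who may approve.** With and/or, approval by the Coordinating Investigator alone, by the IRB alone, or by both satisfies Section 4. The weakest of these is one approval without ethics review.

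**2. What may be waived.** The clause covers any exception to the selection criteria. It shields no criterion, sets no maximum number and asks for no ground. Read literally it reaches even inclusion criterion 4 (written informed consent), which Section 13.3 requires from every subject. That can hardly be intended, but the wording does not prevent it.

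**3. Section 4 against 6.1.1.1.** Section 4 allows enrolment of a patient who fails a criterion. Section 6.1.1.1 requires all inclusion and no exclusion criteria and names no exception. As worded, both cannot be followed for the same patient.

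**4. Section 4 against 8.3.4.** Pregnancy is exclusion criterion 13 in Section 4.2, so Section 4 leaves it open to exception. Section 8.3.4 forbids enrolment after a positive test. This is a direct conflict on a named criterion.

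**5. Section 4 against 12.2.** Section 12.2 requires prior ethics approval of an amendment for any deviation and excepts only the removal of an immediate hazard. Enrolling a patient outside the criteria removes no such hazard. On its natural reading 12.2 therefore excludes what Section 4 allows. Whether a waiver foreseen in the protocol counts as a deviation at all is not stated.

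**6. Effect on the primary estimate.** The plan's own precision figure reproduces: Section 9.1 gives limits of 0.43 and 0.57 for a rate of about 50%, and the exact (Clopper-Pearson) interval for 100 of 200 is 0.429 to 0.571, a half-width of about 7 points.

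If a fraction *f* of treated patients entered by exception, the shift in the rate is *f* × (*p*w − *p*e), where *p*w and *p*e are 1-year survival in waived and eligible patients. The protocol gives neither *f* nor *p*w. For scale only, assume *p*e = 0.50, *f* = 5%, 10% or 20% (10, 20 or 40 of 200), and *p*w = 0.13, 0.25 or 0.70. The first two values of *p*w are the historical 1-year rates that Section 9.1 cites for mucosal and uveal melanoma; the third is arbitrary.

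| *f* | *p*w = 0.13 | *p*w = 0.25 | *p*w = 0.70 |
|---|---|---|---|
| 5% | 0.05 × (−0.37) = −1.9 points | 0.05 × (−0.25) = −1.3 | 0.05 × 0.20 = +1.0 |
| 10% | −3.7 | −2.5 | +2.0 |
| 20% | −7.4 | −5.0 | +4.0 |

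The range runs from −7.4 to +4.0 points, and with no waivers it is zero. Its width comes entirely from the assumptions, so it shows that a shift is possible and says nothing about how large it would be.

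**The case against.** The case on the other side is substantial.

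- **6.1.1.1 refers back to Section 4.** Just before the sentence quoted above, it says that eligibility is determined by the criteria detailed there. One can therefore read 6.1.1.1 as the general rule and the exception clause as part of what it refers to. This softens the conflict but does not remove it: the sentence that follows is unqualified, and 8.3.4 is unqualified as well.
- **A foreseen exception may not be a deviation.** Section 12.2 requires conduct as described in the approved protocol and then restricts what the investigator may do. An exception granted before enrolment, by a route in that protocol, can be read as compliance. This stands as a possible reading, so the conflict with 12.2 is an ambiguity and not a proven contradiction. It has a cost, however: a waiver that is not a deviation falls outside the duty in 12.2 to record significant deviations in the eCRF.
- **The trial wants a broad, daily-practice population.** That is true, but the breadth is already written into the criteria, which admit ECOG 2, uveal and mucosal melanoma and asymptomatic CNS metastases.
- **There is no hypothesis test.** The result is an estimate with a confidence interval, so no success threshold can be crossed by a shift. This limits the consequence.

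A reader might also infer that the primary analysis is itself flawed because waived patients count in it. The protocol does not support that. Analysing all treated patients is sound, and it applies only to waived patients who receive at least one dose. The issue is who may be enrolled, not how they are analysed. Nor does the protocol support a claim that the survival rate will be biased by a given amount or in a given direction, or that any particular kind of patient would in fact be waived in.

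**Conclusion.** The point holds as an inconsistency in who may be enrolled. Section 4 calls its criteria mandatory and then opens every one of them to exception on a single approval that need not come from an ethics committee. That conflicts with 6.1.1.1 as worded and with 8.3.4 on pregnancy. Against 12.2 the position is ambiguous: hard to reconcile on the natural reading, defensible if a foreseen exception is not a deviation.

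The consequence is a less well-defined population behind a single-arm estimate, and a route past the safety exclusions without ethics review. The conclusion rests on the wording alone and needs no assumption about how often the clause would be used. The sections should be reconciled. This is worth doing because it is cheap, not because a large effect has been shown.

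**What to change.** Delete the exception sentence in Section 4. In its place, state that no case-by-case exceptions to the inclusion or exclusion criteria are granted and that a criterion may be changed only by an approved amendment under 12.2. Sections 4, 6.1.1.1, 8.3.4 and 12.2 then say the same thing.

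Add that a patient found to be ineligible after at least one dose stays in the all-treated (ITT) analysis as planned, and is recorded and listed as a protocol deviation. The planned analysis does not change.

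Requiring both approvals, or sending each exception through 12.2, would also bring in ethics review. Either would still leave 6.1.1.1 and 8.3.4 to be reworded and the population open to individual decisions.

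The cost is a sentence or two of protocol text. The downside is that an occasional borderline patient cannot be enrolled.

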### 4.1 Inclusion Criteria

Patients meeting all of the following criteria will be considered for admission to the trial:

1. Histologically proven cutaneous, mucosal or uveal melanoma
2. Measurable disease according to RECIST in unresectable stage III-IV
3. Minimum age of 18 years,
4. Able and willing to give valid written informed consent
5. Must have received at least one line of prior systemic therapy for advanced malignant melanoma resulting in one of the following conditions:
  - a. relapsed following a response of CR, PR or SD or
  - b. failed to demonstrate a response of CR, PR or SD or
  - c. did not tolerate such a regimen due to toxicity.
6. An interval of at least 28 days since treatment with chemotherapy, biochemotherapy, surgery, radiation, or immunotherapy, and recovery from any clinically significant toxicity experienced during treatment is recommended. Prior treatment must be completed by the time of ipilimumab administration. Palliative radiation therapy outside of the brain or therapeutic radiation to the brain after the patient's condition is stabilized and systemic steroids required for the management of symptoms due to brain metastases is decreased to the lowest fixed dose possible and does not require the 28-day waiting period. Patient must have recovered from any acute toxicity associated with prior therapy.
7. Expected survival of at least six months
8. ECOG Performance Status 0, 1 or 2.
9. Within the last 2 weeks prior to study day 1 the following laboratory parameters, which should be within the ranges specified:

| Lab Parameter                   | Range                                                                                                                                    |
|---------------------------------|------------------------------------------------------------------------------------------------------------------------------------------|
| White blood cells (WBC)         | $\geq 2500/\text{mm}^3$ ( $\geq 1.25 \times 10^9/\text{L}$ )                                                                             |
| Absolute neutrophil count (ANC) | $\geq 1000/\text{mm}^3$ ( $\geq 1.0 \times 10^9/\text{L}$ )                                                                              |
| Platelets                       | $\geq 75.000/\text{mm}^3$ ( $\geq 75 \times 10^9/\text{L}$ )                                                                             |
| Hemoglobin                      | $\geq 9 \text{ g/dL}$ ( $\geq 90 \text{ g/L}$ ; may be transfused)                                                                       |
| Creatinine                      | $\leq 2.0 \times \text{ULN}$                                                                                                             |
| Bilirubine total                | $\leq 2.0 \times \text{ULN}$ (excepted patients with Gilbert's Syndrome, who must have a total bilirubin less than $3.0 \text{ mg/dL}$ ) |

ALT, AST

≤ 2.5 x ULN for patients without liver metastasis,  
 ≤ 5 x ULN for patients with liver metastases

10. No childbearing potential or negative pregnancy test of women of childbearing potential performed within 7 days prior to the start of treatment.  
 Women of childbearing potential (WOCP) must be using an effective method of contraception (Pearl-Index < 1, e.g. oral contraceptives, other hormonal contraceptives [vaginal products, skin patches, or implanted or injectable products], or mechanical products such as an intrauterine device or barrier methods [diaphragm, spermicides]) throughout the study and for up to 26 weeks after the last dose of investigational product, in such a manner that the risk of pregnancy is minimized.  
 No men of fathering potential or men of fathering potential must be using an effective method of contraception to avoid conception throughout the study and for up to 26 weeks after the last dose of investigational product, in such a manner that the risk of pregnancy is minimized.

WOCP include any female who has experienced menarche and who has not undergone successful surgical sterilization (hysterectomy, bilateral tubal ligation, or bilateral oophorectomy) or is not post-menopausal. Post-menopause is defined as:

- Amenorrhea ≥ 12 consecutive months without another cause, or
- For women with irregular menstrual periods and taking hormone replacement therapy (HRT), a documented serum follicle stimulating hormone (FSH) level ≥ 35 mIU/mL.

Women who are using oral contraceptives, other hormonal contraceptives (vaginal products, skin patches, or implanted or injectable products), or mechanical products such as an intrauterine device or barrier methods (diaphragm, condoms, spermicides) to prevent pregnancy, or are practicing abstinence or where their partner is sterile (eg, vasectomy) should be considered to be of childbearing potential.

WOCP must have a negative serum or urine pregnancy test (minimum sensitivity 25 IU/L or equivalent units of HCG) at Baseline within 7 days before the start of ipilimumab and at week 12.

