## 5.2 Re-Induction Treatment

Patients who have progressed following stable disease (SD) of  $\geq 3$  months duration from Week 12 assessment OR patients who have progressed following an initial response to the induction treatment (CR or PR diagnosed at week 12 assessment) may be offered additional cycles of therapy (4 infusions of ipilimumab 3mg/kg every 3 weeks) with the originally assigned treatment regimen ("Re-induction") until off-treatment criteria are met, provided they meet re-treatment criteria specified below.

- Re-treatment criteria:

Patients who received ipilimumab as induction in this study and have met each of the following criteria within **28 days** before re-treatment, are eligible for "re-induction":

- Had no unacceptable toxicity requiring ipilimumab discontinuation; OR
  - Patients who did not permanently discontinue treatment due to select irAEs as follows:
    - Reversible autoimmune hepatitis
    - Medically manageable endocrinopathy
    - Reversible dermatological toxicity
  - ECOG performance status of 0, 1 or 2
  - Electrocardiogram (ECG): during screening and week 12. Patients with an existing myocarditis are excluded from this study. For patients with suspicion of myocarditis e.g. dyspnoea, functional insufficiency etc. ECG examinations have to be performed before each treatment.
  - Patient must meet all other inclusion criteria as outlined before (see Inclusion criteria)
- AND
- Have experienced disease progression as documented by physical examination or diagnostic imaging (including brain imaging) after demonstrating expanded clinical benefit (see below).

All patients eligible for Re-induction treatment with ipilimumab their TSH level must be assessed at baseline and before each dose and the TSH level be available to the investigator prior to the administration of the dose. **The assessment of TSH is mandatory prior each treatment.** If a subject has thyroid dysfunction and concomitant symptoms (i.e. fatigue), the subject should be monitored more frequently and be treated as per standard medical practice.

The management algorithm for endocrine abnormalities is available on page 59 (appendix 10-15).

- Re-induction treatment:

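### Inclusion criterion 9 gives two white-cell limits that differ two-fold: 2500/mm³ is 2.5 × 10⁹/L, not 1.25 × 10⁹/L

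*Protocol*

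**What the plan says.** Criterion 9 in Protocol Section 4.1 introduces a table of laboratory limits: "Within the last 2 weeks prior to study day 1 the following laboratory parameters, which should be within the ranges specified". The white blood cell row reads "\geq 2500/\text{mm}^3$ ( $\geq 1.25 \times 10^9/\text{L", a leading figure per mm³ followed by a bracketed figure per litre.

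Three other rows have the same two-unit layout:

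- Neutrophils: "\geq 1000/\text{mm}^3$ ( $\geq 1.0 \times 10^9/\text{L"
- Platelets: "\geq 75.000/\text{mm}^3$ ( $\geq 75 \times 10^9/\text{L" (the point is a thousands separator)
- Hemoglobin: "\geq 9 \text{ g/dL}$ ( $\geq 90 \text{ g/L}$ ; may be transfused"

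Three further statements bear on how the limit is used. Section 6.1.1.1 makes the criteria binding at screening: "Patients must meet all inclusion criteria and none of the exclusion criteria to be considered eligible". Section 5.2 brings them back among the re-treatment criteria: "Patient must meet all other inclusion criteria as outlined before (see Inclusion criteria". The opening of Section 4 allows departures only with prior approval: "Any exceptions from the protocol-specific selection criteria must be approved by the Coordinating Investigator and/or the Institutional Review Board (IRB) before enrollment".

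**The concern.** In the neutrophil, platelet and hemoglobin rows the bracket restates the leading limit in other units. In the white-cell row it does not: it states a limit half as large. The cell therefore holds two different thresholds, and the bracketed one is the more permissive.

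The limit decides eligibility. Investigators apply it locally before online registration (Section 3.2), at up to 26 sites according to the Synopsis. Two sites working in different units could decide differently on the same patient. The exception route in Section 4 does not help, because the text does not say which figure determines whether an exception is needed. A monitor checking source data has the same difficulty in deciding whether a deviation occurred.

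Low counts are plausible in this population. Criterion 5 requires prior systemic therapy, and criterion 6 only recommends the 28-day interval after chemotherapy.

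**Working it through.** **Inputs**, all from the table under criterion 9 in Section 4.1:

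- White cells: 2500/mm³, bracket 1.25 × 10⁹/L
- Neutrophils: 1000/mm³, bracket 1.0 × 10⁹/L
- Platelets: 75 000/mm³, bracket 75 × 10⁹/L
- Hemoglobin: 9 g/dL, bracket 90 g/L

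**Formulas.** 1 L = 10⁶ mm³, so cells per litre = cells per mm³ × 10⁶. For hemoglobin, 1 L = 10 dL, so g/L = g/dL × 10.

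**Each row converted and compared with its bracket**

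| Row | Conversion of the leading figure | Bracket as stated | Bracket ÷ conversion |
|---|---|---|---|
| White cells | 2500 × 10⁶ = 2.5 × 10⁹/L | 1.25 × 10⁹/L | 0.5 |
| Neutrophils | 1000 × 10⁶ = 1.0 × 10⁹/L | 1.0 × 10⁹/L | 1 |
| Platelets | 75 000 × 10⁶ = 75 × 10⁹/L | 75 × 10⁹/L | 1 |
| Hemoglobin | 9 × 10 = 90 g/L | 90 g/L | 1 |

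The white-cell bracket is the only one that does not reproduce. In the other direction, 1.25 × 10⁹ ÷ 10⁶ = 1250/mm³. The two white-cell limits differ by a factor of 2.5 ÷ 1.25 = 2.0.

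**Who falls between the two limits.** These are patients with 1250 to 2499 white cells/mm³ who also meet the neutrophil limit of 1000/mm³. The neutrophil share they need is:

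- at 1250/mm³: 1000 ÷ 1250 = 80%
- at 2499/mm³: 1000 ÷ 2499 ≈ 40%

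The band is therefore possible, but narrow at its lower end.

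**Which figure is meant.** Two things point to 2500/mm³. First, in the other two-unit rows the bracket is the conversion of the leading figure, so the leading figure is the limit. Second, the margin over the separate neutrophil limit is 2500 − 1000 = 1500/mm³ with the leading figure, but only 1250 − 1000 = 250/mm³ with the bracketed one. A white-cell limit that close to the neutrophil limit would be odd.

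**The case against.** The arithmetic is not in dispute; the objection concerns its weight.

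If it is evident that 2500/mm³ is meant, an investigator can see that too, since both figures stand side by side. The slip is then closer to a typographical error in a secondary unit than to a competing rule. The protocol does not say which units local laboratories report, so divergent decisions between sites are a possibility and not a demonstrated problem. This stands as a limit on the likely harm. It does not remove the contradiction, because nothing elsewhere in the protocol tells a site which figure governs.

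The affected group is also narrow. The neutrophil, platelet and hemoglobin limits and the requirement to have recovered from acute toxicity still apply, and hematology results must be reviewed before each dose. The neutrophil limit is consistent in both units and excludes neutropenia below 1000/mm³ on either reading. All of this stands.

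The third point concerns re-induction. Criterion 9 is tied to study day 1, which Section 5.1 defines as the day of the first dose, whereas Section 5.2 uses a 28-day window before re-treatment. One could argue that the white-cell limit does not carry over. But Section 5.2 calls for all other inclusion criteria without excepting the laboratory limits, so carry-over is the fair reading, and the day-1 wording does not defeat it.

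Lastly, the word chosen in criterion 9 is a soft one. Section 4 and Section 6.1.1.1 nevertheless make the inclusion criteria mandatory.

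**Conclusion.** The concern holds. The white-cell limit in criterion 9 contradicts itself by a factor of 2.0, in a binding eligibility threshold that also applies, on a fair reading, before re-induction. The bracketed figure is wrong if the leading figure is the intended limit. That is an inference from the table's layout and from the neutrophil limit, since the protocol does not state it outright.

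The consequence is confined to eligibility and safety screening. The protocol gives no basis for counting patients between the two limits; the number is probably small. Neither the sample size justification nor the one-year survival analysis is affected. The point is worth correcting because the wrong figure is the looser one and the correction is unambiguous, but it does not call the design into question.

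**What to change.** In Section 4.1, criterion 9, change the bracketed white-cell figure from 1.25 to 2.5, so that the row gives a minimum of 2500/mm³ (2.5 × 10⁹/L). The sponsor should confirm that 2500/mm³ is the intended limit when making the change. If the electronic case report form has a range check on this value, it should be checked against the same figure.

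The cost is one number in one table cell, with no change to design or analysis.
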